#### Qualitative in-depth interviews

We will conduct qualitative in-depth interviews with the health care staff involved in providing ACP and with family members/nominated surrogates of deceased patients. In these in-depth interviews, we will examine their views and experiences regarding ACP and why they believe ACP is successful or not in meeting patient preferences for EOL care. This will enable us to identify the strengths and limitations of ACP in Singapore and in tailoring the intervention to address limitations and replicate it in other health care institutions in Singapore and other countries.

## Discussion

This study assesses the impact of ACP in meeting preferences for EOL care among patients with advanced CHF. Until now, this outcome has been evaluated only in one RCT by Detering et al. [14]. However, that RCT was conducted among elderly hospitalized patients with varied diagnoses and not specifically among patients with advanced CHF [14]. Further, we do not know whether the beneficial effect of ACP is also applicable to Asian settings where family caregivers and physicians mostly make decisions for the patient. In addition, the present study will also assess whether ACP lowers health care expenditures, improves quality of life, decision-making and understanding of illness. If the study results show that ACP is effective, this will promote its uptake among health care providers and patients both within Singapore and in other countries.

### Limitations

Attrition may be a problem. We will try to minimize this through appropriate patient incentives and by scheduling interviews at times and places convenient for patients. It is also not possible to execute a double-blinded trial of ACP given that ACP is provided by a multidisciplinary team. Unblinded trials may be prone to bias, such as in assessment of primary outcome. We will attempt to reduce subjectivity in assessment of the outcome by having more than one senior investigator in the study team to review the contents of the medical records and to assess compliance with patients’ wishes as stated in the ACP or the survey documents. Contamination of the control arm is also possible if patients in the control arm seek ACP outside of the trial, during the follow-up phase.

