### Intervention

The patient and their family members will be referred to an ACP facilitator. The ACP facilitator will be certified in providing ACP. Other than assisting individuals in determining their preferences for future medical care, the ACP facilitator will provide emotional support to patients/families with making EOL decisions. Family members will be encouraged to be present during the ACP discussion so that the whole family unit will be able to explore goals, values and beliefs towards the patient’s medical care. With family members’ participation, there is a greater likelihood that they come to understand and support the decisions made by the patient during ACP. Patients will be encouraged to appoint a substitute health care decision-maker who will make the decisions on their behalf when they are no longer able to do so.

The ACP document is dated and specifies whether the patient prefers CPR or not, and whether the patient wants comfort measures only (medications, oxygen and other measures may be used for comfort at the place where the patient lives), limited additional intervention (may include limited trial of treatment, oral/intravenous medications, non-invasive ventilation support and transfer to hospital, if needed) or full treatment (may consider intubation, mechanical ventilation, cardioversion and transfer to intensive care, if needed) as well as any other additional care preferences. Preferred place of medical treatment in the event of deterioration as well as preferred place of death is also noted in the ACP document. The names of substitute decision-makers are specified. A copy of the completed ACP document will be provided to the patient, substitute health care decision-makers and the health care team. The ACP document will be filed onto the front page of the patient’s inpatient case notes and a copy will be scanned into the patient’s electronic medical records in the National IT System, which is shared by all hospitals in Singapore, for easy retrieval and viewing in case the patient is admitted to any hospital in Singapore. This is to ensure that immediate retrieval of the ACP document is possible when treatment decisions must be made quickly.

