### Control arm

The control arm patients will not take part in ACP discussions and documentation, but will continue to receive usual care.

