### Outcome measures

#### Primary outcome

The primary outcome to be assessed in the study is the proportion of patients receiving EOL care consistent with their stated preferences. Patients’ stated preferences for CPR, life-prolonging treatments (comfort measures only/limited intervention/full treatment), place of care and place of death will be assessed from their last survey or their ACP document. The actual treatment received by the patient will be assessed from their medical records after the patient’s death. If these records are unavailable, this information will be assessed in post-death interviews with the patient’s family members/surrogate decision-maker. Actual place of death will be ascertained from death certificates and actual place of care from post-death interviews with the patient’s family members/surrogate decision-maker. The analysis will only be conducted for the sub-group of patients who die during the study period.

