
### Recruitment and data collection

A list of patients with heart failure who are admitted at each center will be sent to the research team daily by heart failure nurses/research coordinators from these centers. The research team will then screen the list for eligibility criteria and approach the patient and family members for participation in the study; those agreeable to participate will be administered a written informed consent form and administered the baseline survey.

Eligible patients who consent to participate in the RCT and answer the survey questionnaires will be randomized to the ACP and control arms. Participants who are randomized into the intervention (ACP) arm will meet with ACP facilitators within 48 hours of consent for intervention delivery. Patients randomized to the control arm will not take part in ACP discussions and documentation, but will continue to receive usual care.

Randomization will be done using block randomization by generating a random allocation sequence of participants to the intervention and control arms through a computerized random number generator. This will be done by a statistician at the institution. The allocation will be concealed in sequentially numbered, opaque and sealed envelopes by the data manager and given to the research coordinator conducting patient recruitment at the two centers. Envelopes will be opened sequentially by the research coordinator only after the participant unique ID is written on the envelope. Randomization sequence will not be known to the research coordinator, health care providers (physicians, ACP facilitators, heart failure nurses) and other researchers involved in the study.

Patients will be followed by the research team for 1 year or until death, whichever is earlier. Further follow-up may be needed if the targeted number of deaths in the intervention and control arms is not reached within the 1-year follow-up period. Patients will be interviewed first at baseline and then every 4 months. At the end of the follow-up period, their medical and billing records will be reviewed to assess the treatment they received and related costs. All questionnaires for both patients and caregivers will be administered in their preferred language from a selection of four: English, Mandarin, Malay, and Tamil. If the patient dies during the study, consenting caregivers will be asked to complete a post-death questionnaire (Fig. 1).

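### The only stated safeguard against biased scoring of the primary outcome is more than one study-team reviewer; masking of these reviewers to arm is not stated, and the notes carry a strong cue to the arm

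*Protocol article*

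**What the plan says.** The Limitations section of the protocol article states "It is also not possible to execute a double-blinded trial of ACP given that ACP is provided by a multidisciplinary team" and then "Unblinded trials may be prone to bias, such as in assessment of primary outcome". Its response is to reduce subjectivity by "having more than one senior investigator in the study team to review the contents of the medical records and to assess compliance" with the patients' wishes "as stated in the ACP or the survey documents".

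Other sections bear on what these reviewers will see:

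- **Primary outcome:** preferences for CPR, treatment level, place of care and place of death "will be assessed from their last survey or their ACP document". Treatment received comes from medical records, or from family interviews where records are unavailable. Place of death comes from death certificates and place of care from family interviews. Only patients who die are analysed.
- **Intervention:** "The ACP document will be filed onto the front page of the" inpatient case notes, and a copy is scanned into the shared electronic record.
- **Control arm:** "The control arm patients will not take part in ACP discussions and documentation, but will continue to receive usual care".
- **Recruitment and data collection:** "Randomization sequence will not be known to the research coordinator, health care providers" and other researchers. This is concealment of the sequence, and it does not concern outcome assessment.

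**The concern.** The article names a specific threat, biased assessment of the primary outcome, and answers it with a measure aimed at something else. Additional reviewers average out individual error. If all of them belong to the team that is testing the hypothesis that ACP improves concordance, and all can recognise the ACP cases, a lean that they share survives any number of readers.

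The reviewers judge compliance directly, with the preference document beside the record. Whether the care given counts as comfort measures only, limited intervention or full treatment needs judgement, because the Intervention section describes the latter two by what they may include. The planned analysis has about 14 ACP deaths, so a few lenient calls on borderline cases could change the primary result.

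**Working it through.** **1. The plan's own numbers (Sample size section).** Inputs: 15% concordance in control, 65% in ACP, 90% power, 95% certainty (taken as two-sided 5%), allocation 1:2.

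- Pooled proportion = (0.65 + 2 × 0.15)/3 = 0.3167.
- n(ACP) = [1.960 × √(1.5 × 0.3167 × 0.6833) + 1.282 × √(0.65 × 0.35 + 0.15 × 0.85/2)]² / 0.50² = (1.117 + 0.692)² / 0.25 ≈ 13.1, rounded up to 14, so 28 in control.
- Patients: 14/0.15 = 93.3, rounded up to 94; 2 × 94 = 188.

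The stated 14 and 28 deaths and 94 and 188 patients reproduce. One ACP death is 1/14 = 7.1 percentage points of that arm's proportion.

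**2. Which items the reviewers can influence.**

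| Item | Source of what happened | Room for reviewer judgement |
|---|---|---|
| CPR | Medical record | Small; largely factual |
| Treatment level (comfort, limited, full) | Medical record | Largest |
| Place of care | Family interview | Not from the record review |
| Place of death | Death certificate | Small |

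**3. How far the arm is visible.** The trial ACP form is in the notes of ACP patients and absent by design in controls. The cue is not perfect: surveys go to both arms, and the Study design section expects that many controls may take up ACP.

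**4. What a shared lean could do.** The documents give no misclassification rate, so the shifts below are assumptions. There is no true difference. The method is exact enumeration of all tables with 14 and 28 deaths: sum the binomial probabilities of the tables with p ≤ 0.05, by uncorrected chi-square and by Fisher's exact test (the analysis section allows chi-square or Fisher).

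| True concordance, both arms | Assumed scoring | Scored ACP vs control | Chi-square | Fisher |
|---|---|---|---|---|
| 50% | no shift | 50% vs 50% | 6.3% | 3.9% |
| 50% | ACP +5 points only | 55% vs 50% | 7.4% | 4.8% |
| 50% | ACP +10 points only | 60% vs 50% | 11.0% | 7.6% |
| 50% | 5 points each way | 55% vs 45% | 11.2% | 7.5% |
| 50% | 10 points each way | 60% vs 40% | 26.4% | 19.7% |
| 15% | no shift | 15% vs 15% | 3.9% | 2.5% |
| 15% | 10% of discordant ACP deaths scored concordant | 23.5% vs 15% | 10.3% | 8.2% |
| 15% | 20% of discordant ACP deaths scored concordant | 32% vs 15% | 24.8% | 19.9% |
| 65% | no shift | 65% vs 65% | 5.6% | 3.7% |
| 65% | 10% of discordant ACP deaths scored concordant | 68.5% vs 65% | 6.0% | 4.2% |

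For the rescored rows, scored ACP = p + (1 − p) × m, for example 0.15 + 0.85 × 0.10 = 0.235. A shift each way opens a gap of twice its size, so 10 points each way is a 20-point gap.

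**The case against.** A reader might infer that the protocol has unblinded investigators scoring the outcome with the arm in view. No sentence says so. The remark about blinding explains why delivery of ACP cannot be masked, and whether the reviewers receive masked extracts is not stated either way. A survey form alone does not reveal the arm, because both arms complete surveys, and a control patient may have an ACP form. These points stand, and the concern is limited accordingly.

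It can also be said that abstraction forms and reviewer masking belong in a full protocol or an adjudication manual, and that the article openly discloses the risk. Silence on masking would indeed be no finding. But the article goes further: it names the bias, states its remedy, and describes reviewers assessing compliance directly. That stated remedy can be judged, and it does not reach a shared lean.

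The sizes are also open to challenge. The 50% base is not one of the protocol's assumed rates, and the largest figure there needs shifts in both arms at once. A 5-point shift in ACP alone barely moves the error rate, and at 65% true concordance the effect of 10% rescoring is slight. The shifts are applied to the whole outcome, although mainly one of its four items is exposed. This stands, and it is why a range is shown with both tests.

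**Conclusion.** The concern holds in limited form. The stated safeguard reduces individual subjectivity but leaves any lean that the reviewers share, and the placement of the ACP form gives a strong though imperfect cue to the arm. The exposure is mainly in the treatment-level item.

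The size cannot be fixed from the documents. Under the assumed shifts, the false-positive rate runs from little change (7.4% by chi-square or 4.8% by Fisher, against 6.3% or 3.9% without a shift) to about a quarter by chi-square and a fifth by Fisher (26.4% or 19.7%; at 15% concordance, 24.8% or 19.9%). These figures assume no true difference, 14 and 28 deaths, and errors that always favour ACP. They show how sensitive the design is and do not predict bias. The change is worth making because it is cheap, and the article reports that the trial is still recruiting.

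**What to change.** Separate the two halves of the comparison, using the same reviewers:

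1. Reviewers abstract care received (CPR, highest treatment level) on a fixed form, from copies of the record with the ACP form, the survey and references to arm removed.
2. Preferences from either source are transcribed separately onto one uniform form, so that the type of document is no longer visible.
3. Concordance is derived from a matching table set in advance. Reviewers do not score compliance directly.

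The Limitations text should then describe this procedure in place of multiple review alone.

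The cost is one abstraction form and redaction of about 42 death records (14 + 28) by existing staff. Sample size and patient care are unchanged. Masking will fail in part where free-text notes mention ACP, and the procedure does not protect items taken from family interviews, since relatives may know the arm.

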### Strengths

The multidisciplinary research team brings the experience required to successfully complete the proposed study. The intervention to be evaluated (ACP) is one of the most promising interventions to promote conversations regarding EOL care between providers, patients and family members. Further, the ACP delivered is a standardized program developed based on the “Respecting Choices Program.” The facilitators are well trained and the environment for program delivery is conducive because of support from hospital staff, physicians and the government.

Lastly, we will also examine the reasons for success or failure of the ACP program in meeting the aims through qualitative in-depth interviews with health care staff and family members/nominated surrogates of the deceased. This will enable us to identify the strengths and limitations of ACP. Thus, the study is expected to have large potential benefit to society and may ultimately lead to improved clinical approaches to the care of patients with advanced CHF at the EOL.

## Trial status

The trial has been approved and is currently recruiting.

## Abbreviations

ACP, advance care planning; CHF, congestive heart failure; CPR, cardiopulmonary resuscitation; EOL, end-of-life; HADS, Hospital Anxiety and Depression Scale; KCCQ, Kansas City Cardiomyopathy Questionnaire
